#### Analytic Considerations

The analysis of the primary outcome will be stratified by cohort (HCT inviters: n=400; CTC inviters: n=200); generalized Hausman tests will evaluate whether the data can be pooled.

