#### Assignment to Study Arms

Participant IDs will be randomly assigned to either arm 1 or arm 2 using a random number generator. The random assignment is expected to result in approximately equal numbers of participants in each study arm.

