### Statistical Analysis

#### Analysis of the Primary Outcome

Efficacy will be analyzed descriptively by comparing, between the 2 study arms, the number of invitees testing for HIV within 1 month per 100 inviters (Figure 3). Analytically, efficacy will be modeled at the level of the inviter, using a zero-inflated negative binomial model, with the number of invitees returning for testing as the dependent variable. The primary explanatory variable will be a binary indicator variable for the study arm. Covariates will characterize variation in invitees’ testing uptake with inviters’ sociodemographic and network characteristics, HIV risk, and stigma.

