#### Sensitivity Analyses

Sensitivity analyses will assess the potential impact of missing data on estimates and describe variation in the acceptability and efficacy of CONSORT by cohort (HCT vs CTC inviters) and gender (male vs female inviters).

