#### Statistical Power

The primary outcome analysis will compare rates of HIV testing among invitees across study arms (Figure 3). As a priori estimates of invitees’ testing rates in the control arm are not known, power calculations for differences in rates between study arms would be speculative. Instead, the power calculations refer to changes in the number of invitees presenting for testing, N_T_, which can be assumed to follow a Poisson distribution with a SE of sqrt (N_T_). Assuming that 20 (alternatively 40, 60, 80, or 100) invitees of arm 2 inviters present for testing, the study has 90% power to detect CONSORT-related differences of 7 (10, 13, 15, or 16) testers between study arms and 80% power to detect differences of 6 (8, 10, 11, or 13) testers between study arms. These calculations apply to cohort- or gender-specific as well as aggregate analyses.

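### A Hausman test on the trial's own data decides whether the primary result is one pooled estimate or two cohort estimates, and the protocol does not say which one tests the hypothesis

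*Protocol article*

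**What the plan says.** Four places in the protocol article bear on this.

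- Analytic Considerations: "The analysis of the primary outcome will be stratified by cohort (HCT inviters: n=400; CTC inviters: n=200", followed by the pooling rule, "generalized Hausman tests will evaluate whether the data can be pooled". The section does not give the level of that test, the coefficients it compares, or what follows if it rejects.
- Analysis of the Primary Outcome: "efficacy will be modeled at the level of the inviter, using a zero-inflated negative binomial model", and "The primary explanatory variable will be a binary indicator variable for the study arm". This describes one model with one arm effect. The legend of Figure 2 likewise presents a single comparison among 600 inviters.
- Sensitivity Analyses: these will "describe variation in the acceptability and efficacy of CONSORT by cohort (HCT vs CTC inviters) and gender (male vs female inviters". Cohort thus appears both as a stratum of the primary analysis and as a topic for sensitivity analysis.
- Statistical Power: the figures are given for 20 to 100 arm 2 testers and are said to hold for cohort-specific and aggregate analyses alike. No significance level is stated anywhere.

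**The concern.** The choice between one pooled estimate and two cohort estimates is made by a preliminary test on the data that will then be used for inference. If the cohorts are kept apart, there are two chances to claim an effect and no stated rule for sharing the error rate between them. Under no true effect, a rejected pooling test also selects trials whose cohort estimates have diverged by chance. Those are the trials in which one cohort is likely to look significant.

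The gate is not needed for validity. Inviters are randomised, so a comparison of all 600 adjusted for cohort is a valid test of the arm effect whether or not the cohorts respond alike. A gate based on few events is also weak evidence: failing to reject would mostly mean that there were too few testers to tell.

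**Working it through.** **The plan's own figures.** The protocol gives no error rate for the pooling procedure. Its only related figures are the detectable differences under Statistical Power, for example "the study has 90% power to detect CONSORT-related differences of 7 (10, 13, 15, or 16) testers between study arms". They could not be reproduced as power: they match z(0.95)·√N (7.4, 10.4, 12.7, 14.7, 16.4 for N = 20 to 100) and, for the 80% series, z(0.90)·√N. That is a separate matter. Only the range of tester counts is used below.

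**Inputs.** From the protocol: 400 HCT and 200 CTC inviters, and roughly equal arms ("The random assignment is expected to result in approximately equal numbers of participants in each study arm"). Assumed: every test two-sided at 5%; pretest on the difference between the cohort arm effects, at 5% unless varied; information 2:1, which follows if testing rates are similar in the two cohorts.

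**1. Type I error.** With inverse-variance pooling, the pooled statistic and the heterogeneity statistic are independent under the null. Hence

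error = (1 − p)·0.05 + p·c,

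where p is the pretest level and c is the chance of a claim given that pooling is rejected. Simulation gives c = 0.668 for the rule that either cohort may be claimed unadjusted. Then 0.95·0.05 + 0.05·0.668 = 0.0475 + 0.0334 = 0.081.

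| Rule when pooling is rejected (pretest 5%) | Type I error |
|---|---|
| Either cohort, unadjusted | 8.1% |
| Either cohort, 2.5% each | 6.9% |
| HCT result only | 5.9% |
| Both cohorts required | 4.8% |

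- Always separate, either cohort unadjusted: 1 − 0.95² = 9.75%.
- Either-cohort rule with a pretest at 10%: 9.4%; at 20%: 10.7%.
- Either-cohort rule (pretest 5%) with an HCT information share of 0.5 or 0.8 instead of 0.67: 8.0% or 8.3%.
- Check with simulated overdispersed counts (200/200 and 100/100 inviters, assumed means 0.2-0.33, robust log rate ratio in place of the zero-inflated model): 8.2-9.0% with the pretest and 9.9-10.7% always separate. Single tests there ran at 5.0-5.9%.
- If the Hausman test compares all coefficients and rejects for reasons unrelated to the arm effect in a fraction q of trials, the either-cohort error is (1 − q)·5% + q·9.75%. For q = 0.5 this is 7.4%.

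**2. Power under a common effect, with the pooled test at 80%.** The expected pooled z is 1.96 + 0.84 = 2.80.

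- HCT alone: 2.80·√(2/3) = 2.29; Φ(2.29 − 1.96) = 63%.
- CTC alone: 2.80·√(1/3) = 1.62; Φ(1.62 − 1.96) = 37%.
- Either, unadjusted: 1 − (1 − 0.628)(1 − 0.366) = 76%. With 2.5% each: 65%.
- Pretest rule with an unadjusted either-cohort claim: 0.95·0.80 + 0.05·0.987 = 81%.

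**3. What the gate can detect.** Take assumed rate ratios of 1.5 in HCT and 1.0 in CTC, with a and b arm 2 testers in HCT and CTC, a:b = 2:1, and Poisson counts. The variance of the difference in log rate ratios is 1/a + 1/(1.5a) + 1/b + 1/b.

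- 40 arm 2 testers (a = 26.7, b = 13.3): variance 0.2125, SE 0.461; z = 0.405/0.461 = 0.88; power 14%.
- 100 arm 2 testers (a = 66.7, b = 33.3): variance 0.085, SE 0.292; z = 1.39; power 28%.

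**The case against.** A condensed article may leave the pretest level, the compared coefficients and the alpha split to an analysis plan that is not shown. That stands, and their absence is not the point here. The point is what the article does commit to: a data-driven gate on the primary analysis, which a faithful analysis plan would inherit.

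Three stronger readings are tempting, and the documents do not support them.

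- A reader might infer that the plan has a type I error of 8-10%. That needs a 5% alpha, a particular pretest level and an unadjusted either-cohort claim, none of which the protocol states. Other rules give 4.8-6.9%.
- A reader might infer that gated pooling loses power. It does not under a common effect: the rule with 8.1% error has 81% power against 80% pooled. The losses belong to cohorts that stay separate, and should not be attached to the pretest rule.
- A reader might infer that nothing about the primary analysis is fixed. The outcome, the 30-day window, the inviter as unit, the model and the arm indicator are all fixed. Only the choice between pooled and separate results is open.

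Two further objections have weight. Describing variation by cohort as a sensitivity analysis is ordinary practice and not an error in itself. And testing clients and people already in HIV care are different index populations with separate recruitment targets, so separate estimates are a legitimate aim. Pooling estimates an effect for a 2:1 mix set by recruitment. That supports reporting both cohorts, and even prespecified separate claims, but not letting a test choose.

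**Conclusion.** The concern holds as a defect in how the primary inference is chosen, with consequences that depend on an unstated rule. The data decide whether there is one primary estimate or two, and the protocol does not say which one answers the study hypothesis. Under the assumptions listed in the working, type I error is about 8% for an unadjusted either-cohort claim after rejected pooling, about 10% if the cohorts are always tested separately, and about 5-7% under stricter rules. Keeping the cohorts separate costs power; the gate as such does not. At 40 to 100 arm 2 testers the gate would miss an assumed contrast of 1.5 versus 1.0 in roughly 72-86% of trials, so a finding that the data can be pooled would say little about whether the cohorts respond alike. The rate ratios, the 2:1 information and all test levels are assumptions, not protocol figures.

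**What to change.** In Analytic Considerations, name the comparison of all 600 inviters, adjusted for cohort, as the single primary test at two-sided 5%, and delete the Hausman gate. Report cohort-specific estimates and the arm-by-cohort interaction as secondary, whatever the pooled result. Align Sensitivity Analyses with this, so that cohort has one stated role. If the investigators do want separate claims for HCT and CTC inviters, say so and split alpha between them in advance, accepting the lower power (for example 65% for either cohort at 2.5% each, where the pooled test has 80%).

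The cost is analysis wording only; design, sample size and data collection are unchanged. The small downside is that cohort-specific results become secondary. The change should be made before any outcome data by arm are seen.

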#### Sensitivity Analyses

Sensitivity analyses will assess the potential impact of missing data on estimates and describe variation in the acceptability and efficacy of CONSORT by cohort (HCT vs CTC inviters) and gender (male vs female inviters).

#### Statistical Power

The primary outcome analysis will compare rates of HIV testing among invitees across study arms (Figure 3). As a priori estimates of invitees’ testing rates in the control arm are not known, power calculations for differences in rates between study arms would be speculative. Instead, the power calculations refer to changes in the number of invitees presenting for testing, N_T_, which can be assumed to follow a Poisson distribution with a SE of sqrt (N_T_). Assuming that 20 (alternatively 40, 60, 80, or 100) invitees of arm 2 inviters present for testing, the study has 90% power to detect CONSORT-related differences of 7 (10, 13, 15, or 16) testers between study arms and 80% power to detect differences of 6 (8, 10, 11, or 13) testers between study arms. These calculations apply to cohort- or gender-specific as well as aggregate analyses.

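### The power figures use a Poisson variance although the primary model allows excess zeros and overdispersion; if counts are overdispersed, the detectable differences are too small and do not carry over to subgroups at the same tester count

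*Protocol article*

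**What the plan says.** In the protocol article, Statistical Power declines to compute power for rates and works instead with the number of invitees who present for testing, "which can be assumed to follow a Poisson distribution with a SE of sqrt" of N_T. The scenarios are set by the control-arm count: "Assuming that 20 (alternatively 40, 60, 80, or 100) invitees of arm 2 inviters present for testing". For these, "the study has 90% power to detect CONSORT-related differences of 7 (10, 13, 15, or 16) testers between study arms", and there is "80% power to detect differences of 6 (8, 10, 11, or 13) testers between study arms". No significance level or sidedness is given. The section closes: "These calculations apply to cohort- or gender-specific as well as aggregate analyses".

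Analysis of the Primary Outcome uses a different distribution for the same outcome: "efficacy will be modeled at the level of the inviter, using a zero-inflated negative binomial model". The modelled quantity is each inviter's count of testing invitees. The section adds covariates for the inviter's sociodemographic and network characteristics, HIV risk and stigma. Analytic Considerations stratifies this analysis by cohort (400 HCT and 200 CTC inviters) and tests whether the cohorts can be pooled.

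**The concern.** A Poisson variance for an arm total requires testers to arrive independently, with no surplus of zero-count inviters and no differences between inviters beyond chance. The protocol's own design points the other way:

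- Social Network–Based HIV Testing Invitations lets one inviter invite contacts across several network dimensions, so testers cluster within inviters.
- Assessment of Secondary Outcomes measures the share of arm 1 inviters who extend at least one SMS invitation, so inviters who send none are foreseen.
- Analysis of the Primary Outcome expects uptake to vary with inviter characteristics.

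If the counts are overdispersed, the true standard error exceeds sqrt(N_T) and the trial is less sensitive than stated. The closing sentence on subgroups is also affected. Under Poisson, sensitivity depends only on the tester count. Under overdispersion it also depends on how many inviters produced that count. A reader could then take a null result in one cohort to be as informative as an aggregate null at the same count, when it is not.

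**Working it through.** **Inputs.** Control counts of 20 to 100 and the printed differences come from Statistical Power. Roughly equal allocation (Assignment to Study Arms) of 600 inviters gives about 300 per arm. The cohorts give about 200 (HCT) and 100 (CTC) per arm, and the gender-balanced sample about 150 per arm for each gender. Alpha is not stated; 0.05 two-sided is assumed. Dispersion is not stated; c = 0.5 to 3 is assumed, the same in both arms.

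**1. The printed figures.** All ten match, after rounding, a multiple of sqrt(N_T) for one count:

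- 1.645·sqrt(N_T) = 7.36, 10.40, 12.74, 14.71, 16.45 (printed 7, 10, 13, 15, 16)
- 1.282·sqrt(N_T) = 5.73, 8.11, 9.93, 11.46, 12.82 (printed 6, 8, 10, 11, 13)

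These are half-widths of two-sided 90% and 80% confidence intervals for a single Poisson count. They contain no separate alpha and power terms and no variance for the second arm. That is a separate error, so the variance question needs a sound benchmark.

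**2. Variance under the primary model.** Let π be the structural-zero fraction, m the mean and α the dispersion of the negative binomial part, and μ = (1 − π)m the overall mean. Then

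Var = (1 − π)(m + αm²) + π(1 − π)m² = μ(1 + cμ), with c = (π + α)/(1 − π).

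For n inviters with total N_T = nμ, the variance is N_T(1 + c·N_T/n). It equals N_T only at c = 0. As an example, π = α = 0.5 gives c = 2.

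**3. Benchmark.** For a two-arm comparison with control count N and difference d:

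SE² = N(1 + cN/n) + (N + d)(1 + c(N + d)/n), power = Φ(d/SE − 1.96) + Φ(−d/SE − 1.96).

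At c = 0, 80% power requires d = 22.1, 29.3, 34.9, 39.6 and 43.7 for N = 20, 40, 60, 80 and 100.

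**4. Worked case: N = 60, d = 34.86, n = 300, c = 2.** The control arm gives 60 × 1.4 = 84.0. Arm 1 gives 94.86 × 1.632 = 154.8. SE = sqrt(238.8) = 15.46, against sqrt(154.86) = 12.44 under Poisson. Power = Φ(34.86/15.46 − 1.96) = Φ(0.295) = 61.6%.

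**5. Power (%) at the benchmark difference.**

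| N_T | n per arm | d | c = 0 | 0.5 | 1 | 2 | 3 |
|---|---|---|---|---|---|---|---|
| 20 | 300 | 22.1 | 80 | 77.7 | 75.5 | 71.3 | 67.4 |
| 60 | 300 | 34.9 | 80 | 74.8 | 70.0 | 61.6 | 54.8 |
| 100 | 300 | 43.7 | 80 | 72.1 | 65.2 | 54.2 | 46.2 |
| 20 | 100 | 22.1 | 80 | 73.4 | 67.4 | 57.5 | 49.9 |
| 60 | 100 | 34.9 | 80 | 65.6 | 54.8 | 40.9 | 32.7 |

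**6. Subgroups.** Two comparisons must be kept apart.

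- *Same testers per inviter.* N_T = 60 from 300 and N_T = 20 from 100 both give 0.2 per control inviter, so the control-arm inflation is identical (1.4 at c = 2). Power is similar: 74.8/70.0/61.6/54.8 against 73.4/67.4/57.5/49.9. The small gap arises because the benchmark difference is relatively larger at the lower count.
- *Same N_T from fewer inviters.* N_T = 60 from 100 is 0.6 per control inviter, and power falls to 40.9% at c = 2. The difference needed for 80% power at N_T = 60 and c = 2 is 45.5, 50.9, 56.4 and 67.9 for n = 300, 200, 150 and 100, against 34.9 for every n under Poisson.

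**The case against.** The strongest reply has four parts.

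- **Choosing the model does not assert overdispersion.** A zero-inflated negative binomial contains the Poisson as a special case, and its covariates may absorb some of the heterogeneity that the marginal formula counts. This stands. A reader might infer that the analysis section assumes the opposite of the power section; it only allows for it. The expectation that c exceeds 0 rests on the design features, and its size is unknown.
- **The subgroup sentence is consistent with its own premise.** The table is indexed by tester count, and under Poisson a smaller cohort simply reads a lower row. This stands too. The sentence is not an independent error; it fails only if the Poisson assumption fails.
- **The CTC loss can be exaggerated.** A reader might infer that the shortfall is greatest in the CTC cohort. That holds only where the same N_T comes from fewer inviters, and the protocol does not suggest that CTC inviters yield three times the aggregate rate. At equal rates the losses are close.
- **The benchmark is not the protocol's.** This is true. If only the variance is changed within the protocol's own construction, at N_T = 60 and 300 per arm, 12.7 becomes 13.4, 14.0 or 15.1 for c = 0.5, 1 or 2. But that construction does not compute power, so a two-arm benchmark is the only meaningful yardstick.

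What remains is that the protocol computes sensitivity under the most favourable case of its own model, gives no reason for doing so, and extends the result to every subgroup.

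**Conclusion.** The point holds conditionally. If per-inviter counts are overdispersed, as the design makes likely, detectable differences built on sqrt(N_T) are too small, and the claim of equal applicability at the same tester count fails. With 300 inviters per arm, the loss from a nominal 80% runs from 2.3 points (N_T = 20, c = 0.5) to about 34 points (N_T = 100, c = 3). At N_T = 60 it is about 5 to 25 points. These sizes rest on an assumed c, two-sided 5% alpha, a normal approximation and unadjusted totals; the protocol fixes none of them.

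It would be tempting to conclude that a better variance would make the printed table right. It would not. Even with exactly Poisson counts, a two-arm test at the printed 90% differences has only 17–20% power. At N_T = 60, for example, Φ(13/sqrt(133) − 1.96) = 20%. That larger fault is separate, and both should be corrected together.

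**What to change.** Rewrite the Statistical Power paragraph:

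- Restate the detectable differences from a two-arm comparison with stated alpha and sidedness and the variance of both arms.
- Use N_T(1 + c·N_T/n) in each arm, or simulate from the zero-inflated negative binomial. Show c from 0 to 3, or a dispersion estimated from the pilot of 100 inviters described in Study Timeline. An estimate from 100 people will be imprecise, so a range should still be shown.
- Replace the closing sentence with separate rows for about 300 (all), 200 (HCT), 150 (each gender) and 100 (CTC) inviters per arm, each at tester counts plausible for that size.

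The cost is a short recalculation and a reworded paragraph. Enrolment and the analysis model are unchanged. The stated detectable differences become less favourable.

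### The ten differences quoted as detectable with 80% or 90% power equal confidence half-widths of a single Poisson count; as two-arm power they are worth roughly 11–21% at two-sided 5%

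*Protocol article*

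**What the plan says.** The Statistical Power section of the protocol article declines to compute power for a difference in rates, because control-arm testing rates are unknown. It works instead with the number of invitees who test, N_T, "which can be assumed to follow a Poisson distribution with a SE of sqrt (N_T").

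It then sets out five scenarios: "Assuming that 20 (alternatively 40, 60, 80, or 100) invitees of arm 2 inviters present for testing". For these it states that "the study has 90% power to detect CONSORT-related differences of 7 (10, 13, 15, or 16) testers between study arms". A second set of smaller differences, for the same five scenarios at the lower power level, follows: "80% power to detect differences of 6 (8, 10, 11, or 13) testers between study arms". The section closes with this statement on subgroups: "These calculations apply to cohort- or gender-specific as well as aggregate analyses".

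The section gives no significance level or sidedness. It does say what is being compared: "The primary outcome analysis will compare rates of HIV testing among invitees across study arms (Figure 3"). Under Assignment to Study Arms, allocation is about 1:1: "The random assignment is expected to result in approximately equal numbers of participants in each study arm". Under Analysis of the Primary Outcome, the efficacy model is fitted at inviter level "using a zero-inflated negative binomial model".

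**The concern.** A detectable difference between two randomized arms must reflect three things: a critical value set by alpha, a further quantile set by the power, and the sampling error of both arms. The stated differences are too small for that. At 20 arm 2 testers, a difference of 7 is only about one standard error of the between-arm difference (7/√47 = 1.02), well short of the 1.96 needed for significance at two-sided 5%.

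This is the article's only statement of the trial's sensitivity on its primary outcome. A reader who trusts it would believe that 27 versus 20 testers, a ratio of 1.35, would be detected nine times in ten. In fact such an effect would usually give a non-significant result, which could then be taken as evidence that the text-message invitations add nothing.

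**Working it through.** **Inputs.** From Statistical Power: Poisson counts with SE √N; arm 2 counts N = 20, 40, 60, 80, 100; differences d = 7, 10, 13, 15, 16 (stated power 90%) and 6, 8, 10, 11, 13 (stated power 80%). From Assignment to Study Arms: about 1:1 allocation. Assumed, because it is not stated: two-sided 5%, with one-sided 5% as an alternative. Arm 1 is taken as the higher arm, the hypothesized direction.

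**Step 1: reproduce the stated figures.** The standard formulas with separate alpha and power terms do not return them, but the half-width z·√N of a single count does.

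| N | 1.645·√N | stated, 90% | 1.2816·√N | stated, 80% |
|---|---|---|---|---|
| 20 | 7.36 | 7 | 5.73 | 6 |
| 40 | 10.40 | 10 | 8.11 | 8 |
| 60 | 12.74 | 13 | 9.93 | 10 |
| 80 | 14.71 | 15 | 11.46 | 11 |
| 100 | 16.45 | 16 | 12.82 | 13 |

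All ten agree after rounding. The multipliers 1.645 and 1.2816 are those of two-sided 90% and 80% confidence intervals.

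**Step 2: power at the stated differences.** With arm 2 mean N and arm 1 mean N + d, the difference has variance N + (N + d) = 2N + d. Power is approximately Φ(d/√(2N + d) − z_alpha). For N = 20, d = 7: 7/√47 = 1.021, and Φ(1.021 − 1.960) = 0.174.

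| N | d (90%) | two-sided 5% | one-sided 5% | d (80%) | two-sided 5% | one-sided 5% |
|---|---|---|---|---|---|---|
| 20 | 7 | 17.4% | 26.6% | 6 | 14.1% | 22.4% |
| 40 | 10 | 18.3% | 27.7% | 8 | 13.4% | 21.4% |
| 60 | 13 | 20.3% | 30.2% | 10 | 13.9% | 22.1% |
| 80 | 15 | 20.4% | 30.5% | 11 | 13.2% | 21.1% |
| 100 | 16 | 19.2% | 28.9% | 13 | 14.2% | 22.5% |

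Exact enumeration at two-sided 5% gives 14.2–18.4% and 11.3–12.9% for the conditional binomial test, and at most 20.6% and 14.5% for the Wald and square-root tests. Across methods, the 90% row is worth about 14–21% and the 80% row about 11–15%.

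**Step 3: differences actually needed.** Solve d = (z_alpha + z_power)·√(2N + d). With k = z_alpha + z_power, d = [k² + √(k⁴ + 8Nk²)]/2. For two-sided 5% and 90% power, k = 1.960 + 1.282 = 3.242.

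| N | 90%, two-sided 5% (ratio) | 80%, two-sided 5% (ratio) | 90%, one-sided 5% | 80%, one-sided 5% |
|---|---|---|---|---|
| 20 | 26.4 (2.32) | 22.1 (2.10) | 23.3 | 19.1 |
| 40 | 34.7 (1.87) | 29.3 (1.73) | 30.8 | 25.5 |
| 60 | 41.1 (1.69) | 34.9 (1.58) | 36.6 | 30.5 |
| 80 | 46.6 (1.58) | 39.6 (1.49) | 41.5 | 34.7 |
| 100 | 51.4 (1.51) | 43.7 (1.44) | 45.9 | 38.4 |

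The ratio is 1 + d/N. At two-sided 5% the needed differences are 3.1 to 3.8 times those stated for 90% power (for example 46.6/15 and 26.4/7) and 3.4 to 3.7 times those stated for 80%.

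**Step 4: overdispersion, as a caveat.** If the variance were φ times the mean, d = (z_alpha + z_power)·√(φ(2N + d)). With φ = 2, which is an assumption and not a figure from the article, 90% power at two-sided 5% needs about 41/53/62/69/76.

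**The case against.** *No alpha is given, so two-sided 5% is imposed from outside.* This is true, and the 11–21% range depends on it. But no conventional choice restores the stated power. One-sided 5% gives about 27–30% and 21–23%. Treating the arm 2 count as known without error gives at most about 51%, even at one-sided 5%. With two Poisson arms, the stated power would need a one-sided alpha of about 0.56–0.60 (90% row) or 0.48–0.50 (80% row).

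*The section is only a set of scenarios, and the 600 inviters are not shown to derive from it.* This stands. It limits the consequence to the stated sensitivity; it does not make the ten figures right.

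*Overdispersion is conjecture.* Partly so. The article names a model that allows for it but gives neither a reason for the choice nor a dispersion estimate. None of the power figures above, nor the needed differences in Step 3, rely on it.

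*Subgroups.* A reader might infer from the last sentence that thresholds for the whole trial are being carried over to cohort and gender subgroups with far fewer testers. The text does not support that as an error. The differences are indexed by the arm 2 count, so the sentence can be read as telling each subgroup to use the row for its own count. On that reading it is sound once the rows are corrected.

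*How the error arose.* It is tempting to say that a confidence level was mistaken for power. The numerical identity is shown; the reasoning behind it is not documented.

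**Conclusion.** The point holds for the ten figures. They coincide with 90% and 80% confidence half-widths of one Poisson count and are not power figures, under the article's own Poisson assumption. At two-sided 5% with two equal arms, actual power is about 14–21% where 90% is claimed and about 11–15% where 80% is claimed. The detectable differences are understated by a factor of 3 to 4. The exact percentages rest on the assumed alpha, on equal allocation and on a Poisson variance; the conclusion that 80% and 90% are not reached does not depend on the choice of alpha. Any overdispersion would make matters worse.

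It does not follow that the trial must be enlarged. The arm 2 count and the true effect are both unknown, so the article gives no basis for calling the trial adequately or inadequately powered. What is wrong is the sensitivity it claims.

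**What to change.** Restate the Statistical Power paragraph:

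- State the significance level and sidedness.
- Replace the ten differences with solutions of d = (z_alpha + z_power)·√(2N + d). For N = 20/40/60/80/100 at two-sided 5%, these are about 26/35/41/47/51 for 90% power and 22/29/35/40/44 for 80%. If one-sided 5% is intended, they are about 23/31/37/42/46 and 19/26/31/35/38.
- Give the matching rate ratios. At two-sided 5% they run from about 2.3 to 1.5 for 90% power and from about 2.1 to 1.4 for 80%.
- Note that overdispersion, which the planned model allows for, would raise these differences, with an illustration such as the φ = 2 row labelled as an assumption.
- Keep the sentence on cohort- and gender-specific analyses, and add that each uses the row for its own arm 2 tester count.

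The cost is one rewritten paragraph and a much less favourable statement of sensitivity. Randomization, outcome, primary model and sample size are unaffected.
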